## Methods/design

### Intervention description

Previous good practices (from different countries) [34, 42] and the opinion of a panel of Portuguese experts was used for the elaboration of a Portuguese cultural-specific adapted model of intervention aiming at the psychological well-being protection and promotion. More specifically, the intervention focuses on the promotion of unemployed individuals’ social, emotional and interpersonal skills. It also targets the strengthening of resilience and of the ability to overcome the adversity of unemployment, by maximizing the personal use of owns’ resources for employability enhancement and future success in re-employment. It is a short-term group intervention (around 20 h, delivered in a two- to three-weeks period) and follows a cognitive-behavioural and psychoeducational paradigm (focusing on mental health literacy). Strategic skills to be promoted are: reduction of mental health related stigma, recognition of psychological suffering (depression and anxiety), coping with depression and anxiety, effective communication and emotional regulation. Regarding the format and structure of the intervention, a maximum of five sessions, three hours each (maximum: 20 persons per group) will be followed.

The intervention was standardized (procedure manual with training and implementation material for facilitators), covering the following modules: Mental health literacy (about depression, anxiety, burnout, emotions), work-life balance, mental health related stigma (personal and perceived stigma), assertiveness training and definition of individual plans of action (defining short, medium and long term goals). Procedures of the intervention will include: roleplays, group discussion of vignettes, emotional and cognitive self-awareness, individual tasks based on cognitive-behavioural intervention (e.g., ABC task for assessing emotions, behaviours and cognitions; self-assessment assertive behaviour grill, for assessing contexts of assertiveness-related difficulties, etc.).

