### Variables in study

Data collection for the controlled community sample will be done for both arms of the trial on three different moments: before the intervention (at baseline), immediately after its ending and three months later.

The indicators for the intervention effectiveness will be: mental health literacy, mental health related personal and perceived stigma, psychological well-being (depression and anxiety), satisfaction with life and resilience. Secondary outcomes include opinions and satisfaction with intervention by intervened unemployed, rate of participation and completion of the intervention. The socio-demographic variables that will be used to characterize the sample and for adjusting outcomes assessment include: age, gender, educational level, previous professional activities, having or not dependent relatives (children, dependent elderly or other relatives to care) and household overall financial comfort.

All questionnaires measuring/assessing constructs (i.e., latent variables) were selected on basis of their psychometric qualities (e.g., internal and temporal reliability, validity) when applied to adult Portuguese general populations. Table 1 provides an overview of the validated instruments that will be included in the effectiveness assessment. Taking into consideration the time usually reported for filling in each of the selected instruments, it is estimated that the total time for filling the complete battery of questionnaires is around 20 min. We will run a pilot test with at least 10 unemployed persons to assess the burden of the questionnaires.

**Table 1 Tab1:** Instruments used in the effectiveness assessment

Assessed constructs	Questionnaire / measure scale	Description
Mental health literacy	Modified/shortened versions of the following instruments:	The DSS is designed to measure stigma associated with depression. It has two subscales which measure two different types of stigma: personal and perceived. Responses to each item are measured on a five-point scale (ranging from zero ‘strongly disagree’ to four ‘strongly agree’). Higher scores indicate higher levels of depression stigma.
	• Depression Stigma Scale (DSS)	
	• Depression Literacy Questionnaire (D-Lit)	

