### Data analysis

Statistical analysis will be carried out using IBM/SPSS 21.0 (or a more updated version, at the moment of the analysis) and R packages. For all tests, the level of statistical significance will be set as α = .05.

For the effectiveness assessment, socio-demographic and outcome variables will be described for each moment of observation. Two strategies of data analysis will be done: (1) intention-to-treat (ITT), as a primary analysis, and; (2) per-protocol, as a supportive analysis. The ITT analysis (treatment as assigned approach), will consider all participants randomly allocated to each arm of the study at baseline with a last observation carried forward imputation for those who did not undergo the final evaluation. The per-protocol analysis (treatment as received approach), will include only the subset of the ITT sample who will completed the evaluations without any major protocol violations. When describing differences between intervention and control group, results from both types of analysis will be reported; for effect size assessment, only per-protocol approach results will be reported, in order to have an estimation of the impact of the treatment as received.

Univariate description of variables will be summarized by central tendency measures (means and medians, according to the normality of their distributions) and respective dispersion measures (standard deviation and range). Normality of data will be assessed through the analysis of kurtosis and skewness.

Association between nominal variables will be assessed through chi-square test (with Yates adjustment, when necessary). Continued variables will be compared (between arms, at the same momentum) by independent samples t-student test or by its non-parametric equivalent (Mann-Whitney test), when adequate.

Effect of the intervention will be studied by linear or logistic regression analysis (according to the nature of the dependent variable), having as dependent variables test-retest variations and adjusting for conceptually (and statistically) relevant variables. Model assumptions will be tested by analysis of residuals and influence diagnostics through Cook’s distance. Cohen’s d coefficient and odds ratio will be used for assessing the size of the intervention effect, when significant.

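### The per-protocol set is presented as treatment as received and is the only source of effect sizes, but its one explicit criterion is completing the evaluations, and it cannot validly estimate the effect of the intervention received

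*Protocol article*

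**What the plan says.** All of this is in the protocol article.

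- **Data analysis, role of the sets.** The two strategies are listed as "1) intention-to-treat (ITT), as a primary analysis, and; (2) per-protocol, as a supportive analysis". Differences between arms are to be reported from both.
- **Data analysis, definition.** The per-protocol analysis, glossed as an as-received approach, "will include only the subset of the ITT sample who will completed the evaluations without any major protocol violations". The article does not say what counts as a major violation.
- **Data analysis, use.** On the size of the effect the text is exclusive: "for effect size assessment, only per-protocol approach results will be reported, in order to have an estimation of the impact of the treatment as received".
- **Variables in study, evaluations.** Data are collected in both arms "before the intervention (at baseline), immediately after its ending and three months later". These are the questionnaire time points.
- **Variables in study, exposure.** Taking part in the sessions is a separate item. The secondary outcomes include "rate of participation and completion of the intervention".
- **Intervention description.** The format is "a maximum of five sessions, three hours each (maximum: 20 persons per group) will be followed". No section gives a number of sessions that counts as having received the intervention.
- **Study design and Ethics.** Controls receive the employment centres' usual care and are offered the intervention later if it proves effective.

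**The concern.** The label and the stated purpose of the set concern exposure to the sessions. The one criterion spelled out concerns returning questionnaires. A person can satisfy either without the other, so a set built on the second need not say anything about the first.

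The label matters because this set alone supplies the reported Cohen's d and odds ratios. A reader will take those figures as the benefit to someone who went through the programme. If the set is really a completer analysis, or a comparison of self-selected attenders with all completing controls, they describe something else. The primary intention-to-treat comparison, which keeps the randomised groups, would have no effect size beside it to show the difference.

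**Working it through.** **1. The article's own figure.** Sampling aspects plans 50 per arm in each of two centres and 30% dropout: 50 × 0.70 = 35, so 70 per arm in total. It states 80% power for an effect size of 0.48. With two-sided alpha 0.05 (sidedness is not stated), 0.48 × √(70/2) = 2.84, and 2.84 − 1.96 = 0.88, which gives 81.1% power (80.5% with the t distribution). The stated figure reproduces. The sample size is not at issue, and 0.48 serves below only as a benchmark.

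**2. Who is in the set under each reading** (intervention-arm participants with no other violation)

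| Participant | Attendance not a violation | Low attendance a violation |
|---|---|---|
| Few sessions, all evaluations | in, counted as treated | out |
| All sessions, an evaluation missed | out | out |
| All sessions, all evaluations | in | in |

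Controls have no sessions to miss, so in the control arm the two readings give the same set.

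**3. Reading A: attendance not covered.** Let f be the share of intervention-arm evaluation completers who attended too little to benefit. Assume that they gain nothing and that the effect in the others is 0.48. The set then shows 0.48 × (1 − f):

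| f (assumed) | Effect shown |
|---|---|
| 10% | 0.432 |
| 20% | 0.384 |
| 30% | 0.336 |
| 40% | 0.288 |

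The proportional loss equals f by construction, so the table shows the mechanism and is not an estimate for this trial.

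**4. Reading B: low attendance is a violation.** Let f now be the share excluded from the intervention arm. Let τ be the effect in adequate attenders, and let δ be the difference in mean outcome without the intervention between people who would attend adequately and those who would not. The intervention arm keeps only the first type, while the control arm keeps both. The set then estimates τ + f × δ. With f at 20% to 30%, the bias is 0.2δ to 0.3δ. It vanishes only if attenders and non-attenders would have had the same outcomes anyway. The documents give neither f nor δ, so its size and direction are unknown.

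**5. Common to both readings.** If the planned 30% dropout occurs and each dropout misses an evaluation, 100 − 70 = 30 people per arm leave the set on that ground, whatever they attended.

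**6. An alternative that keeps randomisation.** The complier-average effect is the intention-to-treat effect divided by the difference between arms in the proportion exposed. Suppose no control is exposed, 80% of the intervention arm is, there is no effect without exposure, and outcomes are complete. An effect of 0.48 in the exposed then gives an intention-to-treat effect of 0.384, and 0.384 / 0.80 = 0.48. Treating the exposed proportion as known, the interval is 1/0.80 = 1.25 times as wide as the intention-to-treat interval (1/0.70 = 1.43 at 70%).

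**The case against.** The strongest objection is that the definition has two conditions, and missing most of a five-session programme is a natural candidate for a major violation. A list of violations commonly sits in the full protocol or SAP, which are not shown, so its absence from an article is no finding. This stands. A reader might infer that attendance plays no part in the set, but the documents do not support that. The point here is different: steps 3 to 5 of the working show that neither way of completing the definition makes the as-received claim valid.

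Second, removing non-adherers from one arm and dropping incomplete records are limits of most per-protocol analyses against usual care, and the article ranks this one as supportive. That is fair, and it limits the consequence. It does not cover the label, or the decision to take effect sizes from this set alone.

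Third, a reader might infer that the published effect will be 20% to 30% too small. The documents do not support this either. They give no attendance rate, the percentage restates the assumed share, and the dilution disappears if low attenders are excluded.

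Fourth, the complier-average estimate has assumptions of its own. In a modular course, people below a completion threshold may still gain something, and the estimate would then be too large. That controls have no access to the sessions during the trial is inferred from the usual-care description. The article lists participation and completion as a rate and does not say that sessions are recorded per person. These objections stand and are carried into the fix.

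**Conclusion.** The concern holds in a limited form. The article claims "in order to have an estimation of the impact of the treatment as received" for a set whose only explicit criterion is completing the evaluations. Whether or not the second condition covers attendance, the set is selected on behaviour after randomisation and does not validly estimate the effect of the intervention received.

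No size can be derived from the documents. The values 0.384 and 0.336 rest on an assumed 20% or 30% of low attenders among evaluation completers, no benefit in them, and none of them excluded as violators. On the other reading the bias is the excluded share times an unknown difference between attenders and non-attenders.

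A reader might also infer that the trial's main comparison is compromised. On this point it is not: intention-to-treat is primary, and arm differences are reported from both analyses. What is affected is the reported effect size and what it is said to mean. That should be corrected before analysis.

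**What to change.** 1. Rename the set as evaluation completers without major violations, state whether major violations include attendance, and drop the as-received claim.
2. Report effect sizes for the primary intention-to-treat analysis. Those from the completer set may stand beside them under the new name.
3. For the effect of treatment received, add a supportive complier-average causal effect. Use randomised arm as the instrument for attendance and the same covariates as the main model. Any attendance or number of sessions is preferable as the exposure. If the sponsor wants a completion threshold, it should be fixed before outcome data are seen. Counting sessions rather than hours also avoids the conflict between the Abstract (four hours per session) and Intervention description (three), which needs to be reconciled separately.

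Steps 1 and 2 cost only wording and reporting. Step 3 costs one further model in R, which is already planned, and a per-participant attendance record. Its downsides should be stated in the plan:

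- The confidence interval is wider.
- It relies on the exclusion restriction: no effect without attendance, no effect below the threshold, or linearity in sessions, depending on the exposure chosen.
- It inherits the missing-outcome handling of the intention-to-treat analysis, here last observation carried forward.
- Binary outcomes need a suitable version, such as a risk difference, because a plain two-stage regression does not give the planned odds ratio.

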**Methods:**

The project follows a RE-AIM-based (Reach, Effectiveness, Adoption, Implementation and Maintenance) framework for assessing a cognitive-behavioural and psychoeducational intervention that has been developed for promoting mental health among unemployed people. It is a short-term group intervention (five sessions, four hours each, 20 unemployed persons per group) focused on mental health literacy, interpersonal communication and of emotional regulation. Implementation of the intervention will be carried out by clinical psychologists, following a standardized procedure manual. Effectiveness will be assessed through a randomized field study with two arms (intervention and control). Participants are unemployed people (18–65 years old, both genders, having at least nine years of formal education) registered at public employment centres from different geographical regions for less than 12 months (including first-job seekers). Allocation to arms of the study will follow a random match-to-case process, considering gender, age groups and educational level. Three moments of evaluation will occur: before intervention (baseline), immediately after its ending and three months later. Main outcomes are mental health literacy, mental health related personal and perceived stigma, psychological well-being, satisfaction with life and resilience. Intention-to-treat and per-protocol analyses will be conducted. Cohen’s d coefficient and odds ratio will be used for assessing the size of the intervention effect, when significant.

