### Sampling aspects

The target population of the HE intervention are unemployed people registered at public employment centres for less than 12 months (including first-job seekers). Random recruitment of participants (for both arms of the study) occurs in two employment centres (from different geographical regions), with match-to-case allocation in arms according to gender, age groups (18–24, 25–44, and 45–65 years old) and educational level (9 to 12, and more than 12 years of completed school – higher education). The full list of the two public employment centres users (with inclusion criteria) will be stratified by gender, age groups and educational level. In each combined stratum, random allocation will be done to each participant who accepts to participate.

Inclusion criteria: unemployed users from public employment centres, 18 to 65 years old, both genders, having at least nine years of formal/public education and being registered in the selected public employment centres at the moment of recruitment.

Exclusion criteria: public employment centres’ unemployed users already attending, at the moment of the recruitment, other public employment centre’s courses, or users with a diagnosed mental or physical severe or incapacitating disease or disability.

Two public employment centres/delegations from two Portuguese regions will be selected (intentional sampling) and invited to participate in the project. The involved public employment centres/delegations differ in terms of size (big dimension vs. small dimension) and type of region (rural population vs. urban population). In each centre/delegation, participants are randomly selected from the full database of users. Allocation to arms is done also in a random way, though following gender, age and educational level strata inter-arms matching.

In each of these settings, the initial (at baseline) users sample size will be of 50 participants with 50 other participants as controls. Previewing a dropout rate of 30% till the end of the project, we estimate to have a final users’ sample size of 35 participants in each of the arms, in each employment centre (70 participants per arm, in total). With this sample size, we expect to have 80% power to detect an effect size of 0,48 in mean scores of mental health literacy, psychological well-being, satisfaction with life and resilience [45].

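### Cohen's d and the odds ratio are planned only for the supportive per-protocol set and only when significant, so the primary ITT analysis has no effect-size measure and the reported ones are inflated by selection on significance

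*Protocol article*

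**What the plan says.** The protocol article, Data analysis, sets out two analyses: "intention-to-treat (ITT), as a primary analysis", with per-protocol as the supportive one. The ITT set is everyone randomised, with last observation carried forward for those without the final evaluation. The per-protocol set is the part of it that completed the evaluations and had no major protocol violation.

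Two reporting rules follow in the same section:

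- Between-group differences are to be given from both sets, but "for effect size assessment, only per-protocol approach results will be reported". The stated reason is to estimate the impact of treatment as received.
- Cohen's d and "odds ratio will be used for assessing the size of the intervention effect, when significant". The abstract (Methods) repeats this: the two measures "will be used for assessing the size of the intervention effect, when significant".

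The article promises no ITT version of either measure, and no effect size for a non-significant outcome.

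**The concern.** These are affirmative rules, not details left to an analysis plan that is not shown, and they pull against the rest of the design. The analysis named as primary yields no effect-size measure, and the supportive one yields the only one. The sample size is justified on a standardised effect, yet the matching d would never be reported from the primary analysis.

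Two separate selections act on the effect sizes that do appear. Membership of the per-protocol set is decided after randomisation, and it may be decided differently in the two arms, since one is offered a course of around 20 hours and the other receives the usual care of the employment centres. The significance condition then removes every small or imprecise estimate. The Discussion section intends the results to inform decision makers, and positive results would lead to an application for further funding. Both uses need an unselected effect size with its interval.

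**Working it through.** **Inputs, all from the protocol article**

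- Significance level: "For all tests, the level of statistical significance will be set as α = .05" (Data analysis). Sidedness is not stated.
- Target: "we expect to have 80% power to detect an effect size of 0,48 in mean scores of mental health literacy" and three other outcomes (Sampling aspects).
- Size per centre: "the initial (at baseline) users sample size will be of 50 participants with 50 other participants as controls" (Sampling aspects). With two centres this is 100 per arm.
- Attrition: "Previewing a dropout rate of 30% till the end of the project" (Sampling aspects). 100 × 0.70 = 70 per arm, so 30 + 30 = 60 of 200 are expected to be lost.

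**Step 1: the plan's own figure.** Power for two means with n per arm is approximately Φ(d√(n/2) − 1.96). With d = 0.48 and n = 70, 0.48 × √35 = 2.840 and Φ(0.880) = 0.81. The noncentral t gives 0.805, and the required n is 69 per arm. The stated 80% reproduces for a two-sided test. A one-sided test would give 0.88 and does not match, so two-sided is assumed below.

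**Step 2: the smallest d that can be reported.** The standard error of d is about √(2/n) = √(2/70) = 0.169. The critical t on 138 degrees of freedom is 1.977. The floor is c = 1.977 × 0.169 = 0.334. Any absolute d below about 0.33 fails the significance condition.

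**Step 3: mean reported d given significance.** With a = (c − d)/SE and b = (c + d)/SE, the normal approximation is

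E[d̂ | significant] = d + SE × [φ(a) − φ(b)] / [Φ(−a) + Φ(−b)].

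For d = 0.30 and n = 70: a = 0.202, b = 3.752, φ(a) = 0.3908, φ(b) = 0.0003, and the denominator is 0.420. The result is 0.30 + 0.169 × 0.3905/0.420 = 0.457. Simulation with an estimated pooled SD (400,000 replicates per scenario) gives:

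| True d | Chance of being reported, 70 per arm | Mean reported d, 70 per arm | Ratio | Mean reported d, 100 per arm | Ratio |
|---|---|---|---|---|---|
| 0.48 | 0.81 | 0.54 | 1.13 | 0.50 | 1.05 |
| 0.30 | 0.42 | 0.46 | 1.53 | 0.40 | 1.34 |
| 0.20 | 0.22 | 0.43 | 2.15 | 0.37 | 1.84 |

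The 100-per-arm columns show the same filter applied to an ITT estimate. Moving to ITT without dropping the significance condition would reduce the inflation but not remove it.

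**Step 4: the per-protocol restriction.** Its effect cannot be computed from the document, so two illustrations on stated assumptions follow.

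- *Selection.* Suppose 30% are excluded and the link between retention and outcome differs between arms by a correlation ρ. The shift in d is ρ × φ(z₀.₃)/0.70 = ρ × 0.497. For ρ from 0.1 to 0.3 this is 0.05 to 0.15 SD, and it takes the sign of ρ.
- *Different quantity.* Suppose completers have d = 0.48 and a fraction f of the intervention arm leaves with no benefit. The ITT value is then 0.48 × (1 − f), which runs from 0.48 at f = 0 to 0.34 at f = 0.30.

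**The case against.** The strongest reply is that the sentence containing the per-protocol rule opens by promising between-group differences from both analyses, and that promise carries no significance condition. Outcomes are also to be described at each time point with measures of centre and spread. A reader might infer from the rule that the randomised comparison goes unreported, or that non-significant outcomes disappear. The document supports neither inference. What is missing is narrower: the ITT effect-size measure, and any effect size for a non-significant result. If ITT means, SDs and group sizes are published, an unadjusted d could even be derived from them.

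A reader might also infer that the per-protocol restriction is bound to bias the effect upwards. That is not established either. The article does not define a major violation or state attendance as a criterion, and the direction depends on who leaves each arm. Part of any gap from ITT reflects the treatment-as-received question that the plan openly poses. Upward bias in magnitude is certain only for the significance filter.

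The figures also depend on choices that the document leaves open. It does not say which test decides significance. It plans covariate-adjusted regression on change, and any precision gained would lessen the inflation. The 30% is dropout by the end of the project, so fewer may be missing immediately after the intervention, while violators would add to the exclusions. At the design effect of 0.48 the inflation is modest.

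These points limit the claim but do not rescue the rule. Wanting a treatment-as-received estimate is a reason to add a per-protocol effect size, not to withhold the ITT one. Neither reply defends reporting only when significant.

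**Conclusion.** The point holds in this limited form. The plan reports ITT differences, but it gives its effect-size measures only for the supportive set and only after passing a significance test. The primary analysis is left without the measure on which the trial was sized.

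The significance filter puts a floor of about 0.33 on any reported absolute d. It inflates the mean reported value by about 13% if the true effect is the design value, and by about 53% to 115% if it is 0.30 to 0.20. These figures assume an unadjusted two-sided test at α = 0.05 with exactly 70 per arm. At 100 per arm, inflation over the same range of true effects is about 5% to 84%.

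The per-protocol value is not protected by randomisation. Its bias is plausibly upward, but neither size nor direction follows from the document.

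**What to change.** Delete the words that make effect sizes conditional on significance, in both the abstract (Methods) and the Data analysis section. Replace the per-protocol-only rule with:

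> Cohen's d or the odds ratio with 95% CI will be reported from the primary ITT analysis for every effectiveness outcome regardless of statistical significance, with the per-protocol value alongside as supportive.

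Both changes are needed, because ITT alone leaves the filter in place. The cost is a few more table columns and some effects that look smaller, with no new data and no change to design or sample size. The ITT effect size will carry any bias from carrying the last observation forward. That is a separate matter, which this change neither creates nor cures.

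### The effect model takes the change score as outcome but does not name the baseline score as a covariate; if it is left out, precision is lost at every plausible correlation

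*Protocol article*

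**What the plan says.** The Data analysis section fits a linear or a logistic model for the intervention effect, depending on the type of outcome, "having as dependent variables test-retest variations and adjusting for conceptually (and statistically) relevant variables". Independent-samples t-tests or Mann-Whitney tests between arms at each time point are listed beside this model.

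The Variables in study section names the adjustment variables: "The socio-demographic variables that will be used to characterize the sample and for adjusting outcomes assessment include: age, gender, educational level, previous professional activities", followed by dependent relatives and household financial comfort. No outcome score is on this list. The same section says that both arms are measured "before the intervention (at baseline), immediately after its ending and three months later", so each scale has a baseline value.

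Under Sampling aspects, the trial starts with 50 + 50 participants in each of two centres, allows for 30% dropout and ends with 70 per arm. On that number, "we expect to have 80% power to detect an effect size of 0,48 in mean scores". That statement mentions neither change scores nor covariates.

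**The concern.** A raw change score subtracts the whole baseline value, which fixes the slope on baseline at 1. When ρ is below 1 and the variances are equal, this is too much. Part of the baseline noise goes into the outcome, and any chance difference between arms at baseline goes into the estimate with the opposite sign. Putting the baseline score in the model lets the data set the slope.

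The article decides the outcome (change) and names some covariates, but not the one that matters most for a change score. A model run with only the named variables would be less precise than the data allow. The power statement concerns mean scores, and an unadjusted change score can be noisier than the follow-up score alone, so the stated 80% might not carry over to the model that will be used.

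**Working it through.** **Inputs.** From the article: α = 0.05 (sidedness not stated), 80% power, standardized effect 0.48 (so SD = 1), 100 per arm at baseline, 30% dropout, 70 per arm at the end. Assumed, because the document does not give it: ρ, shown from 0.2 to 0.9. Equal variances at baseline and follow-up are also assumed.

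**Step 1: the plan's own figure.** For a two-sided comparison of two means, n = 2(1.960 + 0.842)²/0.48² = 68.1, so 69 per arm; the article has 70. Power at 70 per arm is Φ(0.48/√(2/70) − 1.960) = Φ(0.880) = 81.1% (80.5% with the t distribution). Dropout: 70/(1 − 0.30) = 100. The design reproduces as a two-sided test of an unadjusted mean score; a one-sided test would give 88%.

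**Step 2: variances, in units of σ².**
- Follow-up score alone: 1
- Change score without baseline as covariate: 2(1 − ρ)
- With baseline as covariate: 1 − ρ²
- Ratio adjusted/change: (1 − ρ²)/[2(1 − ρ)] = (1 + ρ)/2, so the share saved is (1 − ρ)/2

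**Step 3: numbers for 0.48 SD, with power at 70 per arm and the n per arm needed for 80% power.**

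| ρ (assumed) | Variance, change | Variance, adjusted | Saved | Power, change | Power, adjusted | n, change | n, adjusted |
|---|---|---|---|---|---|---|---|
| 0.2 | 1.60 | 0.96 | 40% | 61.2% | 82.6% | 110 | 66 |
| 0.3 | 1.40 | 0.91 | 35% | 67.0% | 84.5% | 96 | 63 |
| 0.4 | 1.20 | 0.84 | 30% | 73.6% | 87.3% | 82 | 58 |
| 0.5 | 1.00 | 0.75 | 25% | 81.1% | 90.6% | 69 | 52 |
| 0.6 | 0.80 | 0.64 | 20% | 88.8% | 94.4% | 55 | 44 |
| 0.7 | 0.60 | 0.51 | 15% | 95.6% | 97.8% | 41 | 35 |
| 0.8 | 0.40 | 0.36 | 10% | 99.4% | 99.7% | 28 | 25 |
| 0.9 | 0.20 | 0.19 | 5% | >99.9% | >99.9% | 14 | 13 |

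Example at ρ = 0.4: change score, SE = √(2 × 1.20/70) = 0.185, power Φ(0.48/0.185 − 1.960) = 73.6%; adjusted, SE = √(2 × 0.84/70) = 0.155, power 87.3%.

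The change score is noisier than the follow-up score alone when 2(1 − ρ) > 1, that is when ρ < 0.5. This is also about where power drops below 80%.

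**Step 4: chance imbalance.** At 70 per arm the SE of the baseline difference is √(2/70) = 0.17 SD. Given an observed difference D, the unadjusted change estimate shifts by −(1 − ρ)D. A one-SE imbalance at ρ = 0.5 moves it by 0.5 × 0.17 ≈ 0.08 SD, against a target of 0.48.

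**Step 5: carried-forward values.** The intention-to-treat analysis uses last observation carried forward. In the extreme case that all 30% dropouts carry their baseline value (equal means and variances), the correlation becomes 0.7ρ + 0.3: 0.58 for ρ = 0.4 and 0.79 for ρ = 0.7. The saving is then (1 − 0.58)/2 = 21% and (1 − 0.79)/2 = about 10%.

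**Step 6: choice of outcome once baseline is in the model.** In a simulated data set with 70 per arm, the follow-up score and the change score, each regressed on arm and baseline, gave the same arm estimate (0.2625) and standard error (0.1423).

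**The case against.** The strongest reply is that the text does not exclude the baseline score. The covariates are those that are relevant conceptually and statistically, and the named list is of socio-demographic variables and is introduced as non-exhaustive. A reader might infer that the model adjusts for socio-demographics only; the article does not say so. If baseline is added, a linear change-score model is equivalent to analysis of covariance and nothing is lost, so the change score is not in itself the error. A condensed article may also leave the full covariate list to another document.

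This stands as a limit on the point but does not remove it. The article fixes the outcome and names covariates, and baseline is not among them. A choice by statistical relevance would also let baseline enter for some scales or time points and not for others once the data are seen.

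Three further readings are tempting and not supported:
- *That the estimate is biased.* Under randomisation the change-score contrast is unbiased, and regression to the mean affects both arms alike in expectation. Only sensitivity to the imbalance that happens to occur remains.
- *That the sample size already counted on baseline adjustment.* It is calculated for mean scores with no adjustment.
- *That the logistic option means cutting a continuous change into improved or not.* The article ties the type of model to the type of outcome and announces no such cut. The variance formula does not cover logistic models.

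It is also fair that the section assigns the intervention effect to regression rather than to the same-time tests. It does not say outright that the regression alone carries the inference.

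**Conclusion.** The point holds as a precision issue with a simple remedy, and the plan should be changed. Leaving out the baseline score costs (1 − ρ)/2 of the change-score variance, which is above zero for every ρ below 1. For an assumed ρ of 0.4 to 0.7 that is 30% down to 15%, or roughly 21% down to 10% under the extreme carry-forward case.

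Whether the stated power is missed depends on ρ. Below about 0.5 it is; at 0.5 or more it is met without baseline adjustment, and what is given up is precision and protection against chance imbalance. The sizes assume equal variances and use the 70 per arm of the power statement, although the intention-to-treat analysis would include all 100 randomised per arm. They ignore variance explained by the socio-demographic covariates, clustering by intervention group and, apart from Step 5, carried-forward values.

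**What to change.** In the Data analysis section, state that each model for a continuous outcome contains arm, the baseline score of the same scale, centre, and the stratification factors gender, age group and educational level. The dependent variable may be the follow-up score or the change from baseline, since both give the same arm estimate and standard error. Add that this model, and not the same-time t-test or Mann-Whitney test, is the basis of inference.

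The cost is one or two sentences. All these variables are already collected, so no new data or participants are needed, and the sample size can stay as it is.
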